# SAFETY VARIABLES

The safety variables include:

- - post-operative pain (CRF pain scales, post-operative pain medications and CRF16 chronic pain)
  - peri- and post-operative blood loss. (<note to programmer: CRF perioperative blood loss and CRF60)
  - Serious adverse events (note to programmer: CRF70)

Cardiac events (CRF40) and gastro-intestinal events (CRF50).

A Serious Adverse Event (SAE) is defined as any AE that results in death, is life threatening, requires inpatient hospitalization or prolongation of existing hospitalization, results in persistent or significant disability/incapacity, or is a congenital anomaly/birth defect. Drug relationship will be assessed as above.

SAEs will be considered only during the 30 days after the administration of the study product (single administration, first=last).

In the event that a partial Start Date (month/year or year) is available, and month/year or year occurs before that of first treatment dose, the AE is considered as non-treatment emergent. However, if month/year or year occurs on or after the date of first treatment dose, the following cases will be considered:

- if month/year is available and month/year of Start Date >= month/year of first treatment dose, the AE is treatment emergent and Start Date will be estimated as the first day of the month;
- if only year is available and year of Start Date >= year of first treatment dose, the AE is treatment emergent and Start Date will be estimated as Jan. 1 of that year.
- In the event that the Start Date is completely missing, Stop Date will be used to determine when the AE resolved. If the AE stopped before first treatment dose, the AE will be considered as non-treatment emergent; otherwise, if the AE stopped on or after first treatment dose or is ongoing, the AE will be considered as treatment emergent and the Start Date of the event will be estimated as first treatment dose.

The estimated start dates will not be listed.

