### 4.2 Study Events Flow Chart

Table A provides a detailed description of the schedule of events.

Table A: Schedule of events

|  | **Screening** | **Treatment** | **Hospital discharge** | **Follow-up at 1, 2, 5 years** |
| --- | --- | --- | --- | --- |
|  | **D-21 to D0** | **D0** | **D8** | **1, 2, 5 years** |
| Written consent | X |  |  |  |
| Inclusion/exclusion criteria | X | X |  |  |
| Randomization |  |  |  |  |
| Baseline data | X |  |  |  |
| Medications | X |  | X | X |
| Histology |  |  | X | X |
| Hospital discharge |  |  | X |  |
| Follow-up at 1 year |  |  |  | X |
| Follow-up at 2 years |  |  |  | X |
| Follow-up at 5 years |  |  |  | X |
| Chemotherapy |  |  | X | X |
| Radiotherapy |  |  | X | X |
| Chronic pain |  |  |  | X |
| Locoregional recurrence assessment |  |  |  | X |
| Distant metastases |  |  |  | X |
| Tumor biomarkers |  |  |  | X |
| Cardiovascular assessment |  | X | X | X |
| Gastro-intestinal assessment |  | X | X |  |
| Blood loss |  | X | X |  |
| Serious Adverse Event |  | X | X |  |
| Death information | X | X | X | X |
| Unblinding |  | X |  |  |
| Screening Log | X |  |  |  |

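### Partial SAE start dates are imputed with no floor at the dose date, so an SAE classed as treatment emergent can be dated before the single dose and outside the 30-day window

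*SAP*

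**What the plan says.** Three statements in the SAP's Safety Variables section bear on the same date.

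- The window: "SAEs will be considered only during the 30 days after the administration of the study product". Study drug is given once, so there is a single reference date.
- Partial dates. If month and year are known and not earlier than those of the dose, "the AE is treatment emergent and Start Date will be estimated as the first day of the month". If only the year is known and is not earlier than that of the dose, "the AE is treatment emergent and Start Date will be estimated as Jan. 1 of that year".
- Completely missing start date. For an event that is ongoing, or that did not stop before dosing, the rule reads: "the AE will be considered as treatment emergent and the Start Date of the event will be estimated as first treatment dose".

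One further sentence ends the section: "The estimated start dates will not be listed". Section 10.10.1 then tabulates SAEs by treatment group and overall, without saying how the 30-day restriction is applied.

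Table A (section 4.2) has a row "Serious Adverse Event" marked at treatment (D0) and hospital discharge (D8). The follow-up column (1, 2 and 5 years) is blank for that row.

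**The concern.** The partial-date rules class an event as occurring after treatment and, in the same sentence, can give it a date before treatment. The flag and the date then disagree. The SAP does not say which of them decides whether the event falls in the 30-day window.

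If the date decides, the rule removes events that belong in the safety tables. It also treats an SAE with a known month less favourably than one with no start date at all, which can hardly be intended. The SAE-based safety profile is a stated secondary objective (section 3.2). For a single dose at induction of anaesthesia, the first days after surgery are of most interest, and that is where the rule most often produces a pre-dose date. Because imputed dates are not listed, a reader of the listings could not see why an event had dropped out.

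**Working it through.** The SAP gives no figure to reproduce here. The check applies its rules to calendar dates.

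**Inputs from the SAP:** the 30-day window and the three imputation rules (Safety Variables); D0 and D8 (Table A).

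**Assumptions, not in the SAP:** dose dates uniform over four calendar years (2013-2016: 1,461 days, 48 months); true onset uniform over the stated days after dosing.

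**One patient.** Dose on 15 March of a non-leap year, SAE on 17 March (day 2).
- Day missing: start set to 1 March, which is day 1 - 15 = -14.
- Only the year known: start set to 1 January, which is day -(31 + 28 + 14) = -73.
- Start completely missing, event ongoing: start set to 15 March, day 0, inside the window.

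If the SAE had instead begun on 4 April, a missing day would give 1 April, day 17, inside the window. The problem is confined to onsets in the same calendar month (or year) as the dose.

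**Month and year known.** In a month of m days, an onset l days after dosing is dated before the dose when dosing fell on day 2 to day m - l, that is, on m - l - 1 days.
- The share of dose dates that are not the 1st is 1 - 48/1,461 = 0.967.
- For D0-D8, summing over the 48 months gives a share of 1 - 48(l + 1)/1,461 at each l. The mean of l + 1 over l = 0 to 8 is 5, so the share is 1 - 240/1,461 = 0.836.
- For D0-D30, the sum over l within one month is m(m - 1)/2. The 28 months of 31 days give 28 × 465 = 13,020; the 16 of 30 days give 16 × 435 = 6,960; the three of 28 days give 3 × 378 = 1,134; the one of 29 days gives 406. The total is 21,520 out of 31 × 1,461 = 45,291, a share of 0.475.

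**Only the year known.** By the same argument the share at each l is 1 - 4(l + 1)/1,461.
- D0-D8: 1 - 20/1,461 = 0.986.
- D0-D30: the mean of l + 1 is 16, so 1 - 64/1,461 = 0.956.

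| Known part of date | Onset D0-D8 | Onset D0-D30 |
|---|---|---|
| Month and year | 84% before dose | 48% before dose |
| Year only | 99% before dose | 96% before dose |

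A full enumeration of dose dates and lags gives the same values (0.836, 0.475, 0.986, 0.956). No true in-window event is imputed later than day 30.

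**With a floor at the dose date.** An onset in the dose month or year goes to day 0. An onset in a later month or year goes to the first day of that period, which is after the dose and no later than the true onset. Every true in-window event therefore stays within days 0-30, and the share dated before the dose is 0%.

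**Table A.** The window runs to day 30 and the last marked SAE contact before the one-year visit is D8, so 30 - 8 = 22 of the 30 days follow the last mark.

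**The case against.** The strongest reply is that no event need be lost. The SAP explicitly classes these SAEs as treatment emergent, never says that the 30-day restriction is applied to the imputed date, and plans SAE tables that do not display a start date. A programmer who selects on the flag would keep every one of them. This stands: exclusion is a consequence only if the filter uses the date. It does not remove the pre-dose date itself, nor the need to say which variable governs.

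It is also fair that every percentage above is conditional on a missing day or month, that the SAP gives no frequency for this, and that early perioperative events are the least likely to lack a day. The rule is the same in both arms, treatment is blinded and the SAE tables are descriptive. The risk is undercounting and poor reproducibility, not a bias towards one arm.

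Three stronger readings are tempting, and the SAP does not support them.

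- A reader might infer that most partially dated SAEs will be dropped. With the month known and onset spread over D0-D30, the share dated before the dose is just under half, and even those are dropped only under one reading of the filter.
- A reader might infer that the treatment-emergent rule has no upper limit, or that late SAEs will be pulled into the window in numbers. The 30-day sentence just before the rules supplies the limit, and the SAP does not show that SAEs with onset after day 30 are recorded at all.
- A reader might infer from Table A that SAEs are not collected after D8. Table A is a visit schedule, and the reporting period may be set in the protocol, which is not available here. Its blank cells are also not reliable evidence: the randomization row has no mark at all, although section 4.6 places randomization 2 to 4 hours before surgery.

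**Conclusion.** The point holds as a fault in a stated rule. The SAP gives an SAE that it classes as treatment emergent a date before treatment whenever the known month or year is that of the dose and dosing did not fall on its first day. That date conflicts with the 30-day window in the same section and with the section's own handling of wholly missing dates.

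Given a missing day and uniform dose dates, about 84% of onsets on D0-D8 and 48% of onsets over D0-D30 are affected; with only the year known, 96-99%. These are shares of SAEs with partial dates, not of all SAEs. The SAP gives neither the number of SAEs nor the frequency of partial dates, so the effect on the safety tables cannot be sized and may be small. Loss of events further requires that the filter use the imputed date, which the SAP leaves open.

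The difference between Table A and the 30-day window is secondary. It is a matter for reconciliation, not evidence that data are missing.

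**What to change.** In Safety Variables, replace the two partial-date imputations with one rule: when the known month or year is that of the dose, and the stop date is not before the dose, the start is the later of the dose date and the first day of the known month or year. For later months or years, the first day of the known period can stay. Add one sentence stating that the 30-day window is applied to the start date after imputation.

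This extends to partial dates the floor that the SAP already uses for completely missing ones. It has one limit to accept openly: an SAE known only to have begun in the dosing year is placed on the dose date and counted, even if it truly began after day 30. A wider rule that kept every SAE merely compatible with the window would not avoid this over-inclusion.

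Secondarily, check the SAE row of Table A against the protocol's reporting period and make the table and the 30-day window agree.

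The cost is two sentences in the SAP, one line of programming and a check of one table row. The date rule needs no new data.

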# PLANNED STATISTICAL METHODS

Efficacy analyses will be reported overall and split by the treatment groups (ketorolac, placebo). Other specific details on the handling of the particular endpoints are provided below. Full details of the tables, figures and listing that will be produced are given in Appendix I.

<Please confirm whether listings are required in addition to tables and figures>

### 10.1 Patient Disposition

A complete accounting of patient eligibility and treatment allocation will be tabulated overall and by treatment group. The purpose of these tables is to account for patient participation in the analysis populations. Supportive listings will be provided.

### 10.2 Demographic and Baseline Characteristics

Demographic characteristics such as patient age, gender, BMI, histopathology will be tabulated overall and by treatment group for the FAS population. All continuous data will be summarized using descriptive statistics (mean, standard deviation, median, minimum and maximum values). All categorical data will be summarized using frequencies and percentages. Supportive listings will be provided.

### 10.3 Pre-operative, concomitant and post-operative pain medications

Pre- and post-operative pain medications will be tabulated overall and by treatment group for the FAS population. Supportive listings will be provided.

### 10.4 During surgery information

Hemodynamics and peri-operative blood losses will be tabulated overall and by treatment group for the FAS population. Supportive listings will be provided.

### 10.5 Chemotherapy, endocrine therapy, or other anti-neoplastic therapy information

Chemotherapy, endocrine therapy, or other anti-neoplastic therapy information will be tabulated overall and by treatment group for the FAS population. Supportive listings will be provided.

### 10.6 Post-operative radiotherapy information

Post-operative radiotherapy information will be tabulated overall and by treatment group for the FAS population. Supportive listings will be provided.

### 10.7 Pain scales

Pain scales will be tabulated overall and by treatment group for the FAS population at the various timepoints after surgery. Supportive listings will be provided.

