### 3.2 Secondary Objectives

The secondary objectives are as follows:

- To examine the effect of perioperative ketorolac on LFS at 2 and 5 years in high risk breast cancer patients.
- To examine the effect of perioperative ketorolac on Metastasis-Free Survival (MFS).
- To examine the effect of perioperative ketorolac on Overall Survival (OS)
- To examine the effect of perioperative ketorolac on post-operative pain and peri- and post-operative blood loss.
- To determine the safety profile of perioperative ketorolac based on serious adverse events (SAEs)

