# GENERAL STATISTICAL METHODOLOGY

### 7.1 General Statistical Conventions

The following general statistical conventions will be implemented, unless the statistical analysis plan or protocol specify otherwise:

- For continuous variables, descriptive statistics will include the number of subjects (n), mean, standard deviation, minimum, median and maximum. For categorical data, frequency counts and percentages will be presented.
- Analysis of all efficacy and safety variables will be based on observed data
- Day converts to month: use number of days divided by 30.4
- Day converts to year: use number of days divided by 365.25
- If more than one measurement of a parameter is performed during the screening period, then the last of all such measurements prior to treatment will be considered the “baseline” value for that patient.
- All data processing, summarization and analyses will be performed using SAS®, Version 9.4 or later.

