#### 10.9.2 Secondary analyses

The 5 years locoregional RR will be analyzed in a similar way as the primary analysis.

Locoregional RFS, DFS, MFS and OS will be summarized using Kaplan-Meier plots. The Kaplan-Meier estimate of the event times will be presented with 95% confidence intervals. These summaries will be done on the FAS population.

The effect of ketorolac will be assessed by comparing the 2 treatment groups by a log-rank test.

.

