#### 10.10.3 Chronic pain

Pain scales will be tabulated overall and by treatment group. Supportive listings will be provided.

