#### 10.10.4 Post-operative bleeding

Post-operative bleeding will be tabulated overall and by treatment group. Supportive listings will be provided.

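### The secondary objective on pain and blood loss asks for an effect of ketorolac, but the SAP pre-specifies only tables by arm and no between-arm contrast

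*SAP*

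**What the plan says.** Section 3.2 sets this objective: "To examine the effect of perioperative ketorolac on post-operative pain and peri- and post-operative blood loss". It is phrased as an effect to be examined, in the same form as the objectives on LFS, MFS and OS. The objective on serious adverse events is phrased differently, as a safety profile.

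The sections that handle these outcomes say:

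- Post-operative pain scales (10.7): "Pain scales will be tabulated overall and by treatment group for the FAS population at the various timepoints after surgery".
- Pain medication (10.3): "Pre- and post-operative pain medications will be tabulated overall and by treatment group for the FAS population".
- Peri-operative blood loss (10.4): "Hemodynamics and peri-operative blood losses will be tabulated overall and by treatment group for the FAS population".
- Chronic pain (10.10.3): "Pain scales will be tabulated overall and by treatment group".
- Post-operative bleeding (10.10.4): "Post-operative bleeding will be tabulated overall and by treatment group".

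The default for continuous variables in section 7.1 is that "descriptive statistics will include the number of subjects (n), mean, standard deviation, minimum, median and maximum", with counts and percentages for categorical data. These are summaries within a group. Section 10.9.2 is the only place where arms are compared on secondary outcomes, and it covers time-to-event endpoints: "Locoregional RFS, DFS, MFS and OS will be summarized using Kaplan-Meier plots", followed by a log-rank test. Pain and blood loss do not appear there.

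**The concern.** Four secondary objectives ask for an effect of ketorolac. Three of them have a planned comparison of the arms, and this one does not. Pain is a possible benefit of the single dose and bleeding a possible harm, and both will be observed under randomisation and blinding. If the plan is followed as written, neither is reported as a difference with its uncertainty.

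Two practical risks follow. First, section 10.7 refers to several time points without naming a main one, so whoever writes the results can choose which time point, measure and method to stress. Second, two columns of figures without an interval make it easy to read a modest bleeding difference as no difference.

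**Working it through.** **Step 1. Match objectives to methods.**

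| Objective in 3.2 | Wording asks for | Planned between-arm method |
| --- | --- | --- |
| LFS | effect | log-rank (10.9.2) |
| MFS | effect | log-rank (10.9.2) |
| OS | effect | log-rank (10.9.2) |
| Post-operative pain | effect | none; tables in 10.3, 10.7, 10.10.3 |
| Peri- and post-operative blood loss | effect | none; tables in 10.4, 10.10.4 |
| SAEs | safety profile | none; tables in 10.10.1 |

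A table by arm can meet an objective about a safety profile. It does not by itself give an effect.

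**Step 2. What the planned tables would allow.** For a continuous outcome at one time point, section 7.1 supplies n, mean and SD per arm. A crude difference m1 − m2, with standard error sqrt(s1²/n1 + s2²/n2), can be computed from those. A confidence interval for an overall pain difference across time points cannot, because it depends on within-patient correlation, which the tables do not show. Nor can a log-scale or Hodges-Lehmann estimate for skewed blood loss, which needs individual values.

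**Step 3. Which patients.** Sections 10.3, 10.4 and 10.7 use the FAS. Sections 10.10.3 and 10.10.4 fall under 10.10, which uses the Safety Analysis Set. One objective is therefore split over two analysis sets: by randomised arm in the first and by treatment received in the second.

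**Step 4. Precision if a contrast were added.** The SAP gives no precision figure for these outcomes, so there is none to reproduce. Section 4.5 gives 200 patients, 1:1, hence 100 per arm. That number was set for the log-rank comparison and is taken here as given.

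- 95% CI half-width for a mean difference, in SD units: 1.96 × sqrt(2/100) = 0.277.
- Difference detectable with 80% power, two-sided 5%: (1.96 + 0.842) × sqrt(2/100) = 0.396 SD.
- Power at 100 per arm: 29% for 0.2 SD, 56% for 0.3 SD, 81% for 0.4 SD, 94% for 0.5 SD.
- With fewer patients observed, the half-width is 0.292 SD at 90 per arm and 0.310 SD at 80 per arm. The detectable differences are 0.418 and 0.443 SD.

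**Step 5. Illustration on natural scales (assumed inputs, not in the SAP).**

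- Pain score with an SD of 1.5 to 3 points: the half-width runs from 1.5 × 0.277 = 0.42 to 3 × 0.277 = 0.83 points.
- Bleeding recorded as yes/no with a common rate p: the half-width is 1.96 × sqrt(2p(1 − p)/100). This gives 6.0, 8.3 and 11.1 percentage points at p = 5%, 10% and 20%.

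**The case against.** The strongest reply is that the SAP's Safety Variables section lists post-operative pain and blood loss with SAEs and cardiac and gastro-intestinal events, and all of these are tabulated. Description would then be the consistent choice. This has weight, but the SAP does not hold to it. Section 3.2 asks for an effect on pain and blood loss and only for a profile on SAEs. Sections 10.4 and 10.7 use the FAS, which section 6.1 names as the efficacy set, while section 6.3 assigns all safety analyses to the Safety Analysis Set.

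A second reply is that Appendix I, not yet supplied, may contain a difference column. That is possible. But it is announced as templates for tables, figures and listings, and nothing in the text tells a programmer to compute a contrast.

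A reader might go further and infer that the trial cannot answer this objective, or that the uncertainty cannot be stated at all. The SAP does not support that: the tabulated n, mean and SD allow a crude difference and interval at a single time point. What is missing is pre-specification.

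A reader might also infer that precision is known to be useful. It is not. The 0.28 SD figure holds for any trial with 100 complete patients per arm, and no SD, scale range or relevant difference is given. Small effects would probably be missed (29% power at 0.2 SD), and the illustrative intervals for binary bleeding are wide relative to the assumed rates.

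Selective reading of time points is likewise a risk of interpretation. Section 10.7 tabulates all of them, so none is hidden.

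**Conclusion.** The point holds as a gap in pre-specification. The SAP states an objective about effect and fixes a method, tables by arm, that does not deliver one. The choice of measure, time point and estimator is left until after the data are seen. This can be established from the text alone and does not depend on the arithmetic.

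The change is worth making but does not touch the primary conclusion: the DFS analysis is unaffected and no data are lost. The achievable precision for a mean difference, about ±0.28 SD with 80% power near 0.40 SD, rests on 100 per arm, complete data and an approximately normal estimate. It shows that moderate effects could be estimated informatively. It says nothing about whether those effects matter clinically.

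**What to change.** Add to sections 10.3, 10.4, 10.7, 10.10.3 and 10.10.4 a ketorolac-minus-placebo difference with 95% CI for each outcome, as follows.

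- **Post-operative pain scales (10.7):** name one overall summary across time points as the main estimate, for example the average arm difference from a repeated-measures model. Give differences at each time point as secondary. A simpler pre-named summary would also close the gap.
- **Pain medication (10.3):** report post-operative use by arm with a between-arm difference beside the pain scores. The SAP counts medication as part of post-operative pain, and scores can mislead if analgesic use differs between arms.
- **Peri- and post-operative blood loss (10.4, 10.10.4):** difference in means, or a log-scale or Hodges-Lehmann estimate if skewed. State in advance how that choice will be made.
- **Post-operative bleeding and chronic pain (10.10.4, 10.10.3):** difference in proportions only where the item is recorded as yes/no, otherwise a difference on the scale. Section 10.10.3 refers to scales and defines no cut-point.
- **Analysis set:** use the FAS by randomised arm for all these comparisons, and keep the Safety Analysis Set tables as description.
- **Status:** label all of these estimates supportive.

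The cost is a few lines of analysis code and some extra table rows, with no new data. The one drawback is a larger number of secondary estimates, which the supportive label and the single named pain summary keep in check.
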